#### MRI

To identify structural characteristics of the individual brain, MR images will be acquired prior to the intervention (baseline, t_0_) and after the intervention (post, t_2_). The brain MRI will be conducted using a 3-T scanner (Vantage Centurian 3T; Canon Medical Systems, Tochigi, Japan). For brain tissue segmentation, 3D T1- and T2-weighted images with high resolution (voxel size: 0.8 × 0.8 × 0.8 mm^3^) will be acquired [77]. In addition, to identify functional and structural connectivity between widespread brain areas, resting-state functional MRI, and diffusion tensor imaging will be obtained [78]. The 3D T1- and T2-weighted images will be used for the computational modeling (see Computational Modeling subsection).

#### Sample size

A previous study proposed the rules of thumb for estimating the sample size of a pilot study based on the anticipated effect size of the future main trial [79]. According to the proposal, if the future main trial is designed around medium to large effect with 80% power and a two-sided 5% significance, a sample size for the pilot trial is set at 10 in each group [79]. Allowing for a 20% of drop-out rate, we will recruit 12 participants in each group.

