## Methods/design

### Study design

This study is a double-blind randomized controlled pilot trial and was designed according to the Consolidated Standards of Reporting Trials (CONSORT) extension to pilot trials [37]. The study flowchart is shown in Fig. 1. Twenty-four stroke patients will be enrolled and randomly allocated to an active or sham tDCS group. This study will be conducted at Fujita Health University Hospital, Aichi, Japan. All participants will provide written informed consent before participation according to the Declaration of Helsinki of 1964, as revised in 2013. This study has been approved by the Certified Review Board at Fujita Health University (approval No. CR21-029) and registered at the Japan Registry of Clinical Trials (jRCTs042200078).

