### Outcomes

#### Feasibility

Referring to the previous recommendations [52, 53], we will evaluate the feasibility of this pilot study based on the following measures: (1) recruitment and enrollment rates: the proportion of participants who meet the eligibility criteria and provide consent after baseline screening (enrollment rate) and the mean number of participants enrolled in the study per month (recruitment rate); (2) adherence rate: the proportion of completed training hours including individual therapy and self-training of the scheduled hours, which will be used to assess the acceptability of the interventions; and (3) retention rate: the proportion of participants who complete the secondary outcome measurement (i.e., ARAT) from the baseline to follow-up assessments.

These measures will be used as the progression criteria to determine whether to proceed with a future main trial [54]. The criteria are as follows: (1) enrollment rate: more than 30% of screened patients consent to enroll [55]; (2) recruitment rate: more than 0.8 participants are enrolled per month [20% of total target recruitment (5 participants) are enrolled in 6 months]; (3) adherence rate: participants complete more than 90% of scheduled training hours (61 hours on average); and (4) retention rate: more than 80% of enrolled participants (20 participants) with all outcomes until follow-up [30, 56]. If at most three criteria are failed and the issues behind them are manageable, the main trial will proceed with some protocol modifications. If all the criteria are not satisfied, the main trial will not proceed [54, 57]. It should be noted that, although the criteria are determined based on the previous studies and our own experiences, we may need to flexibly reconsider the criterion for the recruitment rate in the case of the COVID-19 pandemic.

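### Twelve per group comes from multiplying 10 by 1.2; it allows for 16.7% drop-out, not the stated 20%, a shortfall of 0.4 participants per group

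*Protocol article*

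**What the plan says.** All references are to the protocol article.

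- **Sample size.** Starting from a published rule of thumb, "a sample size for the pilot trial is set at 10 in each group". The condition attached to that rule concerns the later trial: "if the future main trial is designed around medium to large effect with 80% power and a two-sided 5% significance". The allowance follows: "Allowing for a 20% of drop-out rate, we will recruit 12 participants in each group". The formula behind the allowance is not given.
- **Study design.** The total is the same: "Twenty-four stroke patients will be enrolled and randomly allocated to an active or sham tDCS group".
- **Feasibility (under Outcomes).** The retention criterion for going on to a main trial is "more than 80% of enrolled participants (20 participants) with all outcomes until follow-up".

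**The concern.** Twenty per cent added to 10 is 12, but 20% taken from 12 does not give back 10. The sentence appears to apply the drop-out percentage to the completers wanted, when it belongs to the participants recruited. If so, the protocol names a drop-out rate that its sample size does not cover in expectation.

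What is at stake is the accuracy of a stated sample-size figure. The 10 per group is the only basis given for the size of the pilot, so the allowance built on it should be right. It also matters as a habit. The article plans to use the pilot's ARAT effect size to size the main trial, and the same multiplication carried forward at 20% would under-recruit by 4% (1.20 in place of 1.25).

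**Working it through.** **Inputs**

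- Target per group: 10 (Sample size).
- Drop-out rate: 20% (Sample size).
- Recruited: 12 per group (Sample size), 24 in total (Study design).
- Retention count: 20 participants (Feasibility).

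**Step 1: reproduce the stated figure.** n × (1 + d) = 10 × 1.20 = 12. This gives the protocol's number exactly.

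**Step 2: the usual allowance.** n / (1 − d) = 10 / 0.80 = 12.5, rounded up to 13 per group, or 26 in total with equal groups. The stated figure is one participant per group lower.

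**Step 3: what 12 leaves at 20%.** 12 × 0.80 = 9.6 per group, and 24 × 0.80 = 19.2 in total. The shortfalls are 10 − 9.6 = 0.4 per group and 20 − 19.2 = 0.8 overall. With 13 per group, 13 × 0.80 = 10.4.

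**Step 4: the drop-out that 12 does absorb.** (12 − 10) / 12 = 2/12 = 16.7%.

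**Step 5: whole people.**

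| Lost | Rate | Left |
|---|---|---|
| 2 of 12 | 16.7% | 10 |
| 3 of 12 | 25.0% | 9 |
| 4 of 24 | 16.7% | 20 |
| 5 of 24 | 20.8% | 19 |

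No whole-number loss from a group of 12 lies above 16.7% and at or below 20%.

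**Step 6: agreement with the retention criterion.** More than 80% of 24 is more than 19.2, so 20 people, or 10 per group if losses are balanced. This is the count in the Feasibility section.

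**Step 7: chance of keeping 10 or more.** This assumes that each participant drops out independently with probability 0.20. The model is an assumption made here and is not in the article.

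| Recruited per group | One group keeps ≥ 10 | Both groups keep ≥ 10 |
|---|---|---|
| 12 | 0.558 | 0.558² = 0.312 |
| 13 | 0.747 | 0.747² = 0.558 |

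The chance of missing 10 in at least one group is therefore 69% with 12 and still 44% with 13. About 25 percentage points separate the two designs. The remaining 44 are chance variation, which inflating to an expected value does not remove.

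**The case against.** The best defence reads the 20% as a ceiling on the loss actually seen. People drop out whole, so a group of 12 that loses no more than 20% loses at most 2 and keeps 10. On that reading 12 is adequate, and the 20 participants in the Feasibility section fit it. A gap of 0.4 of a person is also within what most readers would call rounding. The point about whole people stands. It does not rescue the sentence as a planning statement, because a drop-out allowance is normally an expected rate, and at an expected 20% the design leaves fewer than 10.

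Three stronger readings are tempting, and the article does not support them.

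- *The trial cannot deliver the size it needs.* The 10 is a rule of thumb, and the 80% power and two-sided 5% level quoted beside it belong to the future main trial. The primary outcomes here are feasibility rates with confidence intervals, and retention is one of the quantities being estimated. No result of the pilot turns on 10 as against 9 or 9.6.
- *The 31% chance that both groups keep 10 measures the cost of the error.* It does not, because a correctly inflated 13 per group reaches only 56% under the same model.
- *The retention criterion conflicts with the sample size.* It does not: 20 is the right whole number for more than 80% of 24. The criterion is a standard for success and makes no assumption about drop-out.

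**Conclusion.** The point holds as a minor correction. The allowance was computed as 10 × 1.2, where 10 / 0.8 was needed. Twelve per group covers 16.7% drop-out, and at an expected 20% it falls short by 0.4 per group, or 0.8 across the trial.

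The conclusion assumes that the 20% is an expected share of those recruited, and that drop-out means the complement of retention as the Feasibility section defines it. If the authors meant a ceiling on whole-person losses, 12 suffices and only the wording needs tightening. On either reading the size of the pilot is not in doubt, and no power statement, analysis or progression criterion changes.

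**What to change.** Keep 24 participants and replace the allowance sentence with wording such as: *Twelve participants per group allows for 16.7% drop-out (2 per group), leaving 10 per group.* The cost is one sentence and a slightly less generous stated allowance. No participants are added, and the text then agrees with the 20 retained participants in the Feasibility section.

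The alternative is to recruit 13 per group and keep the 20%. That would change the total of 24 in the Abstract and Study design. It would also move the retention count (more than 80% of 26 is more than 20.8, so 21) and require the recruitment benchmark to be rechecked (20% of 26 is 5.2, against the 5 now given). The gain does not seem worth those edits.

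If probabilities of keeping 10 per group are quoted, give 12 and 13 side by side (31% and 56% for both groups) and state the assumption of independent 20% drop-out. For the main trial, divide by one minus the drop-out rate.

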#### Blinding

Participants, assessors, occupational therapists providing intensive upper limb training, experimenter applying the tDCS, and a researcher analyzing the data will be all blinded to group allocation. Independent researchers who will conduct the random allocation will not be blinded. A researcher who is in charge of patients’ safety, and risk management can access the group allocation via the REDCap if necessary. To quantify the success of blinding, we will ask participants which group they think they were allocated after the intervention period.

#### Analytical methods

The feasibility outcomes will be reported with descriptive statistics. Recruitment, enrollment, adherence, and retention rates will be calculated with a 95% confidential interval. Furthermore, adverse events and their frequency will be recorded. If there are some exclusions or dropouts, the reasons and the step at which they occur will be recorded. For the potential side effects of tDCS, the median score for every 14 items of the questionnaire regarding symptoms will be calculated. Regarding the success of blinding, the percentage of correct guesses will be reported.

The active and sham tDCS groups will be compared with regard to demographic variables to assess group differences using the Student’s *t* test or Mann-Whitney *U* test for continuous variables and the *χ*^2^ test for categorical variables. Group differences of the ARAT, FMA, and MAL-14 scores and neurophysiological measures outcomes will be analyzed using multivariable regression analyses and compared at each assessment time point. To evaluate the efficacy of the present pilot study, an effect size of the ARAT score will be computed, which will be used to determine the sample size for the future main trial.

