### Interventions

A time schedule of this study is shown in Fig. 2A. The participants will be admitted to Fujita Health University Hospital. The participants will receive individual therapy of intensive upper limb training for 4 h per day (2 h per half-day) and engage in self-training for 2 h per day (1 h per half-day) and receive cerebellar tDCS (active or sham) for 20 min at the beginning of the intensive training (Fig. 2B), considering that the effects of tDCS on the neural excitability of a targeted brain region last for 30–120 min [2, 5–7]. This will be repeated for 5 consecutive days per week for 2 weeks (i.e., 10 days of intervention). During the intervention period, botulinum toxin injections and any changes of medications that could affect spasticity will not be allowed.

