#### Safety evaluation

To evaluate the safety of the intervention and overall protocol, we will record adverse events such as burns to the skin, prolonged abnormal cutaneous sensation, dizziness, fatigue, and pain related to overuse of the affected arm. To monitor the existence of the temporary side effects, especially of the tDCS, we will provide participants with a questionnaire [58] after every 20 min of active or sham tDCS intervention. The questionnaire consists of 14 items regarding symptoms which will enable us to determine if the participants are experiencing severe symptoms. The score ranges from 1 to 10, from absent to severe symptoms.

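### The median item score for the tDCS symptom questionnaire can read 1 (absent) while up to 5 of 12 participants in an arm score severe, so it cannot show how often severe symptoms occur

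*Protocol article*

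**What the plan says.** The Safety evaluation section introduces the questionnaire as the means of monitoring temporary side effects, those of tDCS in particular: "we will provide participants with a questionnaire [58] after every 20 min of active or sham tDCS intervention". It has 14 symptom items, "which will enable us to determine if the participants are experiencing severe symptoms". On the scale it says: "The score ranges from 1 to 10, from absent to severe symptoms".

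Under Interventions, stimulation is given on five days in each of two weeks, so a participant who completes treatment fills in the form 10 times.

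Under Analytical methods, the summary named for these data is that "the median score for every 14 items of the questionnaire regarding symptoms will be calculated". No count, percentage, range or maximum is named beside it. The same paragraph says separately that adverse events will be recorded with how often they occur.

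**The concern.** The scale has its floor at absent, and the questionnaire is meant to reveal severe symptoms. A median describes the middle participant. If more than half of the participants do not have a given symptom, the median is 1, and it is 1 whether the others score 2 or 10. The statistic is therefore insensitive to the part of the distribution that the questionnaire is there to show.

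The Discussion says that the pilot's findings will inform whether to proceed to a main trial and whether to redesign the protocol, including the dose of the interventions. A table of fourteen medians, most or all equal to 1, would tell that decision little about tolerability. It could be read as an absence of symptoms when it shows only that fewer than half of the participants had each one.

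**Working it through.** **Inputs from the Protocol article**
- Scale: 1 = absent, 10 = severe (Safety evaluation).
- Sessions per participant: 5 × 2 = 10 (Interventions).
- Group size: "a sample size for the pilot trial is set at 10 in each group", then "Allowing for a 20% of drop-out rate, we will recruit 12 participants in each group" (Sample size).

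**The plan's own figure.** The article gives no figure for the symptom summary, so the figure to reproduce is the group size on which each median rests. Adding 20% gives 10 × 1.20 = 12, as stated. Dividing by the retained fraction gives 10 / 0.80 = 12.5, or 13, which is close enough not to matter here. Both 12 (full arm) and 10 (completers) are used below.

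**How many severe scores the median can hide.** Take one score per participant on one item, with k participants at 10 and the other n − k at 1. For even n, the median is the mean of the ordered values in positions n/2 and n/2 + 1. It equals 1 when position n/2 + 1 still holds a 1, that is, when n − k ≥ n/2 + 1, or k ≤ n/2 − 1. For odd n the condition is k ≤ (n − 1)/2.

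| Participants in the arm | Largest k with median 1 | Share | Median with one more severe score |
|---|---|---|---|
| 12 | 12/2 − 1 = 5 | 5/12 = 41.7% | (1 + 10)/2 = 5.5 |
| 11 | (11 − 1)/2 = 5 | 5/11 = 45.5% | 10 |
| 10 | 10/2 − 1 = 4 | 4/10 = 40.0% | (1 + 10)/2 = 5.5 |

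The result does not depend on where severe begins. Any score above 1 in place of the 10 leaves the median at 1 for the same k.

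**How often this would happen.** The article gives no expected symptom rate, so the rates here are assumptions. Let p be the true proportion with a severe score on an item, and let all other participants score 1. In an arm of 12 the median is 1 when X ≤ 5, with X ~ Binomial(12, p):

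P(X ≤ 5) = Σ C(12, x) pˣ (1 − p)¹²⁻ˣ, summed over x = 0 to 5.

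| Assumed p | P(median = 1) |
|---|---|
| 0.10 | 0.999 |
| 0.20 | 0.981 |
| 0.30 | 0.882 |
| 0.40 | 0.665 |

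Under these assumptions, an item rated severe by one participant in five would almost always be reported with a median of 1.

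**What the added summaries would show.** In the case of 5 severe scores among 12, the median reads 1. The count reads 5/12 (41.7%) and the largest individual maximum reads 10.

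**The case against.** The strongest reply is that detection and summary are different things. The form is completed after every session, and severe symptoms can be seen by reading each form as it comes in, whatever statistic is tabulated at the end. Adverse events are recorded separately with their frequency, and the examples listed (burns, abnormal skin sensation, dizziness, fatigue, overuse pain) overlap with what a symptom form would pick up. Reasons for dropout are recorded, and a researcher responsible for safety can see the allocation. A median is also a conventional summary of an ordinal item, and nothing says that no other statistic will be given.

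Much of this stands, and it limits the point. It does not remove it: no stated rule turns a high questionnaire score into an adverse event, so the adverse event table need not contain what the questionnaire found. The article also commits to one particular statistic for these data, and that statistic is poorly matched to symptoms that most participants lack.

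Three stronger readings are tempting, and the article does not support them.
- **That nearly half of the evidence can be hidden by pooling sessions.** If all 12 × 10 = 120 sessions in an arm were pooled, 59 of them (49.2%) could be severe with a median of 1. The article does not say that sessions are pooled, or how the ten are combined. The size is therefore stated per participant, at 40% to 42% for 10 or 12 in an arm.
- **That the arms will be merged.** The sentence does not mention arms, but silence in a condensed article is not a plan to pool, and the next paragraph compares active with sham.
- **That a tolerability problem would pass unrecognised into the main trial.** That would require the separate adverse event record and the review of individual forms both to miss it.

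**Conclusion.** The point holds as a weakness of the questionnaire summary. With one score per participant and the remaining scores at 1, the named median stays at absent with up to 5 of 12 participants in an arm (42%), or 4 of 10 completers (40%), at the severe end. It therefore cannot show how often severe symptoms occur. The probabilities of 88% to 98% for true rates of 30% to 20% rest on assumed rates and illustrate the point only.

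It is not a failure of the trial's safety reporting as a whole, because adverse event frequencies are reported by a separate route. No primary feasibility outcome, progression criterion or hypothesis test is affected. It is a cheap improvement to a descriptive safety table, worth making because that table may inform the design of the main trial.

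**What to change.** Keep the per-item median and add, for each of the 14 items and for each arm under a coded label so that the analyst stays blinded:
- the number and percentage of participants with any score above 1 at any session;
- the number and percentage with any score in a severe range, which the sponsor states before the data are examined (the article defines no such range, and this review does not propose one);
- each participant's maximum score over the 10 sessions, shown as a listing or a distribution.

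Taking each participant's maximum first also avoids having to decide how repeated sessions are averaged. The cost is one sentence in Analytical methods and a few table rows. No new data, visits or participants are needed.

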In stroke rehabilitation, intensive task-oriented training is crucial for facilitating motor recovery. Constraint-induced movement therapy (CIMT) is a well-known approach for improving upper limb motor function after stroke. The key element in CIMT is that it encourages the use of the affected arm through intensive functionally oriented tasks [27, 28]. Although it is generally accepted that neural and functional recovery reaches a plateau around 6 months after stroke onset [29], reviews have shown the effectiveness of CIMT in post-stroke survivors in the chronic stage [30, 31]. In addition, several stroke guidelines highly recommend CIMT as a beneficial approach for improving upper limb motor function and activity especially in the chronic stage [32, 33]. Furthermore, studies reported that CIMT combined with tDCS [34, 35] or combined with tDCS and the peripheral electrical stimulation [36] of motor-related cerebral regions induced greater effects on upper limb motor function compared to CIMT alone.

In view of these, we hypothesized that a combination of cerebellar tDCS and intensive movement therapy would further facilitate the improvement of motor function in stroke patients in the chronic stage. To clarify this hypothesis, we designed the present study to assess (1) the feasibility of a study that will examine the effects of cerebellar tDCS combined with intensive upper limb training and (2) the preliminary effects of this combined approach on upper limb motor function. The present study details a pilot trial that will be conducted before a large-scale randomized controlled trial.

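### The main trial is to be sized on the ARAT effect observed in about 10 patients per arm, an estimate too imprecise for that use

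*Protocol article*

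**What the plan says.** The rule is the last sentence of Analytical methods: "an effect size of the ARAT score will be computed, which will be used to determine the sample size for the future main trial". It carries no qualification. The Discussion adds, more loosely, that the findings will help in redesigning the protocol, sample size included.

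The Sample size section takes the pilot's own size from "rules of thumb for estimating the sample size of a pilot study based on the anticipated effect size of the future main trial". The condition is "if the future main trial is designed around medium to large effect with 80% power and a two-sided 5% significance", and the result is that "a sample size for the pilot trial is set at 10 in each group". It then states: "Allowing for a 20% of drop-out rate, we will recruit 12 participants in each group". The Feasibility section sets the retention target at "more than 80% of enrolled participants (20 participants) with all outcomes until follow-up", again about 10 per arm.

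The Background describes the efficacy aim as "the preliminary effects of this combined approach on upper limb motor function". Analytical methods plans 95% intervals for the feasibility rates but mentions none for the ARAT effect size. Neither that section, Sample size nor the Discussion names an important ARAT difference, a confidence limit, shrinkage or outside evidence to temper the observed effect.

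**The concern.** A pilot of this size can estimate a standard deviation or a retention rate well enough to plan with. It cannot do the same for a treatment effect. Required sample size varies with the inverse square of the effect, so the error in the effect is magnified when it is turned into a number of patients. An estimate that is too high by chance gives a main trial too small to detect the real effect. One that is too low by chance gives a trial far larger than needed, and an estimate at or below zero gives no sample size at all. At stake is the power and cost of the main trial.

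**Working it through.** **Inputs from the protocol article.** 10 evaluable per arm, 20% dropout, 12 recruited per arm (Sample size); 24 patients in two arms (Study design); 20 retained (Feasibility); main trial at 80% power and two-sided 5% for a medium to large effect (Sample size).

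**Assumptions.** The article gives no number for medium to large. I take d = 0.5 to 0.8, with 0.2 and 0.3 as sensitivity values. Outcomes are normal and unadjusted for baseline.

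**Step 1: the plan's own figure.** 10 × (1 + 0.20) = 12 per arm, 24 in total, as stated. Dividing instead gives 10 / 0.80 = 12.5, so 13 per arm. The gap is small and is not part of this point. The base figure of 10 comes from a cited rule of thumb and cannot be re-derived from the article.

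**Step 2: precision of the observed effect.** SE(d) = √(2/n + d²/(4n)), with n = 10 per arm:

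- d = 0.5: √(0.2 + 0.25/40) = 0.454
- d = 0.8: √(0.2 + 0.64/40) = 0.465

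Exact noncentral-t 95% intervals:

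| Observed d | 10 per arm | 12 per arm |
|---|---|---|
| 0.5 | -0.40 to 1.38 | -0.32 to 1.31 |
| 0.8 | -0.12 to 1.70 | -0.04 to 1.63 |

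**Step 3: what those limits mean for the main trial.** n per arm = 2 × ((1.96 + 0.84)/d)², rounded up. This gives 63 at d = 0.5 and 25 at d = 0.8. The upper limits with 10 per arm (1.38 and 1.70) give 9 and 6. The lower limits are negative, so no finite n follows.

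**Step 4: applying the rule repeatedly.** 200,000 simulated pilots per setting, 10 per arm, with each observed d put into the formula of step 3:

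| | True d = 0.5 (63 needed) | True d = 0.8 (25 needed) |
|---|---|---|
| Observed d ≤ 0, no usable n | 13.1% | 3.6% |
| n less than half the needed | 33.2% | 25.1% |
| n more than double the needed | 23.6% | 25.7% |
| **Sum of the three rows** | **69.9%** | **54.4%** |
| n within 25% of the needed | 11.1% | 18.5% |
| Planned n per arm, 10th to 90th percentile (d > 0) | 12 to 660 | 8 to 168 |
| Mean true power (d > 0) | 65.2% | 72.5% |

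**Step 5: sensitivity** (share with no usable n or one wrong by more than a factor of 2).

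- Smaller true effects, 10 per arm: about 82% at d = 0.3 and 88% at d = 0.2.
- All 12 per arm retained: about 67% at d = 0.5 and 50% at d = 0.8.
- Hedges' small-sample correction, 10 per arm: about 69% at d = 0.5 and 53% at d = 0.8.

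**Step 6: the alternative.** With 18 degrees of freedom the 95% interval for the SD is 0.76 to 1.48 times the estimate. The one-sided 80% upper limit is √(18/χ²₀.₂₀,₁₈) = 1.18 times. Using that limit raises 63 to about 88 per arm and 25 to about 35. The error in the SD can be covered by a modest, known inflation; the error in the effect cannot.

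**The case against.** The best defence is that this is a feasibility pilot. Its primary outcomes are rates, its efficacy aim is labelled preliminary, and nothing in its conduct, safety or primary analysis depends on the sentence. The main trial will need its own justification of size, and the Discussion's wording is softer than a mechanical plug-in. That stands as an argument about severity. It does not remove the point, because Analytical methods states the rule outright.

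The planned regression could also help. Adjustment for baseline could give a larger standardised effect and somewhat less mis-sizing. The article gives no correlation, so I have not put a number on this.

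Several stronger readings are tempting, and the article does not support them:

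- **That a low estimate would stop a useful treatment, or that only pilots with promising estimates go forward.** The Feasibility section bases progression on enrollment, recruitment, adherence and retention. No ARAT result is among the criteria.
- **That Sample size and Analytical methods contradict each other.** The first uses a provisional effect band to choose the pilot's size. Intending to refine that band with data later is not a contradiction, although 10 per arm is too few to refine it with.
- **That leaving open the time point or the choice of SD is itself an error.** Such detail is commonly left to an analysis plan, which is not shown here.
- **That the choice between a raw and a baseline-adjusted SD would more than double the effect size.** The ratio is 1/√(1 - r²), which passes 2 only when r exceeds about 0.87. The article gives no r.

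**Conclusion.** The point holds as a should-fix. The stated rule sizes the main trial on an estimate with a standard error of about 0.45. At 10 completers per arm it would more often than not give no usable sample size or one wrong by more than a factor of 2: about 70% of the time at a true d of 0.5 and 54% at 0.8. With no dropout the figures are about 67% and 50%, so in the most favourable case the chance is about even. Where the estimate is positive, mean true power falls to about 65% to 72%.

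These figures rest on reading medium to large as d = 0.5 to 0.8 and on normal, unadjusted outcomes. The 0.5 results alone would overstate the problem if the true effect is large, so both ends should be quoted. The consequence is a mis-sized main trial, not a flaw in the pilot's feasibility assessment.

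**What to change.** Replace the last sentence of Analytical methods with wording such as:

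> The main trial will be sized on a pre-specified minimum important ARAT difference. The pilot will supply only the ARAT SD (for example its one-sided 80% upper confidence limit, 1.18 times the pooled SD on 18 degrees of freedom), the correlation between baseline and follow-up, and attrition. The pilot ARAT effect will be reported with its 95% confidence interval, as description only.

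The factor of 1.18 applies to 10 completers per arm; with all 12 per arm it is 1.16. The change is best made before the pilot results are seen, since a favourable estimate would be hard to set aside afterwards. It costs wording only. The downside is that the planned main trial may be larger than one based on a favourable pilot estimate.
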